	**Study period**										
**Timepoint**	**Enrolment**	**Baseline**	**Allocation**	**Post-allocation**							**Pre-/post-allocation**
		**t**_**0**_		***t***_**1**_ **First meeting**	***t***_**2**_ **2 months**	***t***_**3**_ **4 months**	***t***_**4**_ **8 months**	***t***_**5**_ **12 months**	***t***_**6**_ **24 months**	***t***_**7**_ **Last meeting**	***t***_**8**_ **During the study**
**Enrolment**											
Eligibility screen	X										
Informed consent	X										
Allocation			x								
**Interventions**											
Early assessment team (EaT)			x								
TAU			x								
**Assessments**											
Demographic data		x						X		x	
WSAS		x			x	x	x	X	x		
CORE-OM		x						X	x		
QPR-15		X			x	x	x	X	x		
WHO-5		X			x	x	x	X	x		
AUDIT		X						X	x		
DUDIT		X						X	x		
EQ-5D-5L		X			x	x	x	X	x		
ISI		X			x	x	x	X	x		
WAI				X							
SRS				X							
Questionnaire for therapist				X						x	
CORE-10					x	x	x				
CSQ										x	
Review of hospital medical records		x						x			x
Review of medication use		x						x			x
Register data from Norwegian Labour and Welfare Administration											x
Qualitative interviews											x

*WSAS* Work and Social Adjustment Scale, *WHO-5*, World Health Organization Well-Being Index, *CORE-OM* Clinical Outcome Routine Evaluation, *AUDIT* Alcohol Use Disorders Identification Test, *DUDIT* Drug Use Disorders Identification Test, *EQ-5D-5L* Euro Quality of life, *QPR* Questionnaire Process of Recovery, *SRS* Session Rating Scale, *WAI* Work Alliance Inventory, *CSQ-8* Client Satisfaction Questionnaire

### Assessments

#### Primary outcome measure

The study’s primary outcome is change in perceived function from baseline to 12-month follow-up, measured by the *Work and Social Adjustment Scale* (WSAS; [52]). This is a self-report questionnaire with five items covering the current situation’s influence on work, on home management, on social and private leisure activities, and on relationships with others. The items are scored from 0 to 8, with a total score ranging from 0 to 40; lower scores indicate better adjustment. The scale has been found to have high internal reliability and sensitivity to change. In addition, a positive correlation has been found between WSAS and the grading of depressive symptoms [52]: a mean WSAS score of 25 coincides with major depression (measured by the Hamilton Depression Rating Scale), a mean score of 15.5 corresponds with mild to moderate depression, and a mean WSAS of 6.5 indicates subclinical symptoms. WSAS has also been found to be sensitive in measuring the effect of treatment [53].

#### Secondary outcome measures

##### Self-reported data

Symptoms of psychological distress are measured using the *Clinical Outcome in Routine Evaluation Outcome Measure* (CORE-OM; [54]), a self-administered questionnaire with 34 items concerning the preceding week, mapping four main areas: subjective well-being (four items), problems/symptoms (12 items), social functioning (12 items), and risk to self or to others (six items). All are scored from 0 to 4. The short version, CORE-10 [55], is used instead of the CORE-OM at the assessment points between baseline and the main outcome at 12 months (i.e. T2–T4 + T6). Both CORE-OM and CORE-10 have shown good psychometric properties [55, 56].

Quality of life is assessed using the *World Health Organization Well Being Index* (WHO-5; [57]), one of the most widely used measures of subjective psychological well-being as well as a measure of depression. The scale consists of five simple and non-invasive questions about participants’ well-being, experienced during the preceding 2 weeks, with items rated on a 6-point scale from 0 to 5. A review demonstrated that the questionnaire has excellent psychometric properties [58].

The *Questionnaire about the Process of Recovery* (QPR-15; [59]) is used to capture perceived improvement. The scale was developed in collaboration with service users and has been widely used to capture people’s accounts of their recovery from severe mental illness. The 15-item version has been recommended for use in both routine clinical work and research, and it is scored on a 5-point scale from 0 to 4. Its psychometric properties, specifically its internal consistency, test re-test reliability, and convergent validity, were found to be high [60, 61].

The *Alcohol Use Disorders Identification Test* (AUDIT; [62]) and the *Drug Use Disorders Identification Test* (DUDIT; [63]) examines problematic use of alcohol and drugs during the preceding 12 months. The AUDIT consists of 10 questions assessing the frequency of drinking, average amount of alcohol consumed, worries of others, harm to oneself and others, inability to function without alcohol, and alcohol-induced memory loss; the answers are summed to a total score of 0 to 40 points. The instrument is widely used and gives reliable results [64]. The DUDIT consists of 11 questions, with a total score of 0 to 44 [63]. In addition to items addressing the amount and frequency of use and the signs of dangerous use or addiction, the participant is asked what drugs they use, including illegal drugs and abuse of prescription drugs. The psychometric properties are considered good [65].

The *Euro Quality of life* (EQ-5D-5L; [66]) is used to measure health outcomes and to perform health economic analyses. The scale was originally intended as a supplement to other quality of life measures, but it is increasingly used as an independent instrument. The five component scales consist of questions related to walking, personal care, daily chores, pain or discomfort, and anxiety or depression. In addition, the participant is asked to indicate their subjective state of health on a *Visual Analogue Scale (VAS)* from 0 to 100. The EQ-5D-5L has exhibited excellent psychometric properties across a broad range of populations, conditions, and settings [67].

Patient satisfaction is assessed using the *Client Satisfaction Questionnaire* (CSQ-8; [68]). The form consists of eight questions regarding quality of the service, offers received, and general satisfaction. It is scored using a 4-point scale, *resulting in total scores of 8* to *32*, *with highest scores indicating a greater level of satisfaction*. The CSQ-8 has been widely used in research and is a shorter version of the original 18-item version [69]. The Norwegian CSQ-8 has been reported as having good reliability and construct validity [70].

The *Working Alliance Inventory Short form Revised* (WAI-SR; [71, 72]) is a self-report questionnaire measuring the therapeutic alliance in three domains: agreement with the therapist on the goals of treatment, tasks required to achieve treatment goals, and the quality of the bond established between the patient and the therapist. The 12 items are rated on a 7-point scale ranging from ‘never’ to ‘always’. Higher scores indicate a stronger therapeutic working alliance, and total scores above 36 represent a positive alliance. The WAI-SR has demonstrated adequate psychometric properties [73]. The questionnaire will be administred to the participants at T1, which contains no other secondary measures for patients than the SRS (see below).

*The Session Rating Scale* (SRS; [74]) is used to elicit further information about how the patient experiences their first meeting with the therapist. The four-item self-report measure maps the goals and topics of the conversation, the relationship with the therapist, the therapist’s approach, and a general perception of the meeting. The structure of the SRS is based on a brief visual analogue scale (VAS), where the patient indicates a score on a continuous ten-point scale. The SRS was designed for use by clinicians to assess the therapeutic alliance during treatment, so that the therapist can change their approach or style if the client reports a negative experience. The SRS has solid reliability, sufficient validity, and high feasibility [74]. In this study, the questionnaire is administred to the participants at T1.

Self-reported demographic data at baseline (T0) also includes information about perceived history of cognitive function. Some questions from the *Rapid Assessment of Potential Intellectual Disability* (RAPID; [75]) are used, namely functioning at school, and whether the person has had learning difficulties or received adapted teaching at school. In the demographic data, we also ask if there are problems in different areas of life (e.g. housing, work and education, family relationships, accidents, etc.) and the extent to which the patient and therapist believe this affects the patient’s present functioning and symptoms. The form is based on findings from a Norwegian multicentre study of CRTs [76] and was also used in the pilot study evaluating the first 2 years of the EaT being operational [5].

##### Therapist-reported data

Data from the therapists are reported after the first interview (T1) and at the end of contact or treatment at the CMHC (T7), through questionnaires developed for this study. The aim is to collect information from the therapists about the sessions, the interventions, and their judgement of the patients’ current mental condition, social functioning, and external stressors affecting the current situation. In addition, the therapists fill in the *Health of the Nation Outcome Scales* (HoNOS; [77]), a 12-item scale originally developed to capture the health and social functioning of people with severe mental illness. The scale assesses external factors which may affect function and condition, and each item is scored from 0 to 4.

##### Medical record data

Participants’ medical records are screened to discover contacts with both mental and somatic specialist health services. From these records, ICD-10 diagnosis in previous and current contacts, and prescribed medication 12 months after the first assessment, will be registered.

##### Register data

Register data from the Norwegian Labour and Welfare Administration will be used to obtain an overview of sick leave and work-oriented activity. We are collecting data up to 12 and 24 months after the time of referral, with the options of collecting data up to 5 years after referral and 3 years before. Relevant variables include medical benefits for income compensation—such as sickness benefit, work assessment allowance (AAP), and disability benefit—as well as more direct measures for return to work and work inclusion.

### Qualitative interviews

The qualitative interviews will be individual and semi-structured. The purpose of the first interview (after the first or second session) is to learn more about how the first encounter with EaT was experienced. The interview will focus on topics such as how the interviewee experienced the conversations with and treatment from the EaT, expectations before meeting with the team, and whether the patient felt that they received sufficient help for what they were referred for. In the second interview (for those who receive follow-up with the EaT over three sessions or more), the purpose is to reveal patients’ experiences regarding EaT treatment over some time. The focus will be on how the follow-up was experienced, what was most useful or not useful, and whether the patient received help for what they had been referred for. In a further qualitative sub-project of the study, it may also be relevant to interview external partners (such as GPs, primary mental health care workers, and carers) who have interacted with the EaT in various cases; the implementation of such a sub-project depends on available resources and capacity, and it is not definitively planned.

### Fidelity

Data collection is carried out as part of ordinary clinical activities. Neither the intervention EaT nor the standard follow-up (TAU) is standardised; consequently, measuring fidelity to an established treatment model is not possible. The therapist provides thorough descriptions, number of interventions provided, and potential collaboration with other agencies during treatment; this information is supported by data from the medical records, collected 12 months after inclusion.

### Power and sample size calculation

In previous studies using the WSAS comparing new psychological treatments with TAU, the standard deviations for WSAS scores were observed to be between 7 and 10 [78–80]. For patients with obsessive compulsive disorder or depression, a WSAS total score of 20–40 is reported to indicate moderate to severe psychopathology, a score of 10–20 is associated with failure in functional level but not with severe symptoms, while scores less than 10 are not associated with clinical populations [52]. In addition, a difference of 3.2–4.8 between intervention groups and TAU at the last follow-up was found in the studies mentioned above [78–80].

Both conditions in our study receive interventions from the specialist mental health service; therefore, we chose to define the clinically significant difference between the two groups in mean change on the follow-up measurement at 12 months post-inclusion to be at least three units of the WSAS total score. In order to have a statistical power of 80% to detect a difference in total WSAS scores of three units, with a *t*-test using a standard deviation of ten units for the total WSAS scores, we need 176 in each group (given a significance level of 0.05). If we estimate a drop-out of 40%, we thus need 294 in each group (176/0.6 = 294). This gives a total sample size of 588.

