### Statistical analyses

The primary analysis of the outcomes will involve the 12-month time point (change in outcome from baseline to 12-month follow-up). A *t*-test will be performed to compare the randomised groups in terms of the primary outcome (WSAS) as well as the secondary outcomes; this test will be conducted within the framework of linear mixed models (LMM) based on data from all time points. Changes over time will also be estimated from the LMMs. If the assumptions for using LMMs are not met, the analyses can be carried out as separate comparisons at the 12-month follow-up. Due to the large sample, independent-sample *t*-tests can be considered according to the central limit theorem. Non-parametric tests will be used if they are considered more appropriate after the distribution of the data is inspected. The assumption of normal distribution for the residuals of the LMMs will be assessed using visual inspection of histograms and normal QQ plots. Due to the method for parameter estimation (maximum likelihood), the LMMs allow for missing outcome data at one or more occasions as long as data are missing at random (MAR); thus, data from all individuals will be included in the primary analyses.

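### The power calculation uses the SD of WSAS total scores for an outcome defined as change, so it silently assumes a baseline-to-12-month correlation of 0.5 at SD 10

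*Protocol article*

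**What the plan says.** Three places in the protocol article put the primary question on change. Under Primary outcome measure, the "primary outcome is change in perceived function from baseline to 12-month follow-up". Under Power and sample size calculation, the target is a "difference between the two groups in mean change on the follow-up measurement at 12 months post-inclusion to be at least three units" on that scale. Under Statistical analyses, "The primary analysis of the outcomes will involve the 12-month time point (change in outcome from baseline to 12-month follow-up").

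The calculation itself is on another scale. It seeks "statistical power of 80% to detect a difference in total WSAS scores of three units" and reaches its number "using a standard deviation of ten units for the total WSAS scores, we need 176 in each group", with alpha set at 0.05. The SD comes from earlier studies in which "the standard deviations for WSAS scores were observed to be between 7 and 10". Dividing 176 by 0.6 for 40% drop-out gives 294 per group and 588 in total.

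The primary test is to sit within a linear mixed model (LMM) using all time points. The article does not say whether baseline is an outcome with free group means, an outcome with means constrained equal, or a covariate. If the model's assumptions fail, the groups may be compared separately at 12 months.

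**The concern.** The SD of a difference between two measurements is not the SD of one measurement. It depends on how strongly baseline and 12-month scores correlate, and that correlation appears nowhere in the article. Pairing a 3-unit difference in change with the SD of total scores is correct only at one value of rho. Below that value a change-score comparison has less than the stated 80% power; above it, more.

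The change contrast is also the less efficient choice. In a randomised trial both arms have the same expected baseline, so adjusting for baseline targets the same treatment effect with smaller variance for any rho below 1. What is at stake is whether 80% is a floor or rests on an unstated number.

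**Working it through.** **Inputs from the article:** difference 3; SD 10 (cited range 7–10); alpha 0.05; power 80%; 176 analysed and 294 randomised per arm; 40% drop-out. **Assumptions, not in the article:** a two-sided test, equal SD at both times, rho, and the drop-out pattern.

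**1. The article's figure.** The normal approximation gives 2 × (1.960 + 0.842)² × 10² / 3² ≈ 174.4, so 175. The noncentral t gives 175.4, so 176. Then 176 / 0.6 = 293.3, so 294, and 2 × 294 = 588. The stated numbers reproduce with a two-sided test and an SD of 10.

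**2. What that SD implies for change.** SD of change = SD × √(2(1 − rho)). Setting this to 10 with SD 10 gives 2(1 − rho) = 1, so rho = 0.5.

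**3. Simple analyses, 176 per arm, SD 10** (baseline-adjusted residual SD = SD × √(1 − rho²)):

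| rho | SD of change | Power, change t-test | Adjusted SD | Power, baseline-adjusted |
|---|---|---|---|---|
| 0.3 | 11.83 | 66.0% | 9.54 | 83.7% |
| 0.4 | 10.95 | 72.6% | 9.17 | 86.5% |
| 0.5 | 10.00 | 80.1% | 8.66 | 90.0% |
| 0.6 | 8.94 | 88.1% | 8.00 | 93.9% |

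The variance ratio, adjusted to change, is (1 − rho²) / (2(1 − rho)) = (1 + rho)/2, which is 0.75 at rho 0.5. At rho 0 the adjusted analysis has 80.1% power, so at SD 10 it does not fall below 80%.

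**4. Other SDs in the article's range.** The change t-test keeps 80% when SD × √(2(1 − rho)) ≤ 10, that is rho ≥ 1 − 100/(2 SD²): 0.38 at SD 9, 0.22 at SD 8, and below 0 at SD 7 (no shortfall for any rho ≥ 0).

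**5. The planned LMM, SD 10, 294 per arm.** If all drop-outs contribute baseline only, m = 0.6 × 294 = 176.4 per arm have 12-month data, and the variance of the contrast is:
- free baseline means: 2 × 100 × [(1 − rho²)/m + (1 − rho)²/294]
- constrained baseline means: 2 × 100 × (1 − rho²)/m

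At rho 0.3, free: 200 × (0.91/176.4 + 0.49/294) = 1.365, SE 1.168, power Φ(3/1.168 − 1.96) = 73%. Constrained: 200 × 0.91/176.4 = 1.032, SE 1.016, power 84%.

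Gradual drop-out reaching 40% at 12 months, under compound-symmetric or autoregressive correlation, does slightly better. Across these patterns:

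| rho | Free baseline | Constrained baseline |
|---|---|---|
| 0.3 | 73–76% | 84–87% |
| 0.4 | 78–82% | 87–90% |
| 0.5 | 84–88% | 90–93% |

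With free means, 80% is reached near rho 0.4 (0.43 in the least favourable pattern). Constraining baseline gains about 6 to 11 points.

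**The case against.** A reader might infer that the 80% power holds only if rho is at least 0.5, or that the trial is underpowered. The documents support neither.

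- The 0.5 threshold is exact only for a change-score t-test on 176 per arm at SD 10. The planned analysis is an LMM using everyone's data, where the threshold is nearer 0.4 even with free baseline means.
- SD 10 is the cautious end of the cited range. At SD 8 and rho 0.3, the change t-test already has 84% power.
- The article gives no WSAS correlation, so a low rho cannot be called likely.
- The LMM may be meant to constrain baseline. That detail could sit in an analysis plan that is not shown, and there would then be no shortfall. A fallback comparison of 12-month totals would also match the SD used.

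All of this stands, and it limits the size of the point. It does not remove the mismatch: the published calculation defines its target on change and takes its SD from totals, without the assumption that links them. An unseen plan would not correct that sentence. If the fallback were run on the declared change outcome, the 0.5 threshold would apply directly at SD 10.

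**Conclusion.** The point holds as an unstated assumption and an avoidable loss of efficiency. It shows neither a power shortfall nor bias, and N reproduces. At SD 10 the calculation implies rho = 0.5. Over rho 0.3 to 0.6, power for a change-score t-test runs from 66% to 88%, against 84% to 94% with baseline adjustment. In the LMM with free baseline means, power is about 73–76% at rho 0.3 and reaches 80% near 0.4; constraining baseline lifts it to 84–87% and 87–90% at those values. These figures rest on assumed rho, equal SDs at both times and assumed drop-out patterns, so they are ranges. It should be changed because the better contrast uses WSAS values already being collected.

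**What to change.** - State the primary contrast as the EaT minus TAU difference in WSAS at 12 months, from an LMM with baseline means constrained equal (no group effect at T0) or with T0 WSAS as covariate. Do the same for secondary scales with a T0 value.
- Restate the power sentence: 80% applies to a 12-month total score with SD 10 and 176 analysed per arm, and is a lower bound for the baseline-adjusted analysis (84–94% at rho 0.3–0.6). If a change contrast is kept, state the assumed SD of change or rho.
- If the constraint is already intended, one sentence saying so is enough.

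The cost is wording, with N unchanged at 588. The article says outcome data from T2 to T6 will not be analysed until inclusion is complete, so the contrast can be fixed without knowledge of results if done before then.

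There is one small downside. The T0 questionnaires go out after consent and stay open for 14 days, and randomisation also follows consent. The schedule table places baseline before allocation, but the text does not make T0 completion a condition of it. T0 values entered after allocation should not serve as baseline, so a few may have to be treated as missing. The constrained LMM keeps those patients; a covariate model would need imputation.

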### Statistical analyses

The primary analysis of the outcomes will involve the 12-month time point (change in outcome from baseline to 12-month follow-up). A *t*-test will be performed to compare the randomised groups in terms of the primary outcome (WSAS) as well as the secondary outcomes; this test will be conducted within the framework of linear mixed models (LMM) based on data from all time points. Changes over time will also be estimated from the LMMs. If the assumptions for using LMMs are not met, the analyses can be carried out as separate comparisons at the 12-month follow-up. Due to the large sample, independent-sample *t*-tests can be considered according to the central limit theorem. Non-parametric tests will be used if they are considered more appropriate after the distribution of the data is inspected. The assumption of normal distribution for the residuals of the LMMs will be assessed using visual inspection of histograms and normal QQ plots. Due to the method for parameter estimation (maximum likelihood), the LMMs allow for missing outcome data at one or more occasions as long as data are missing at random (MAR); thus, data from all individuals will be included in the primary analyses.

The sample size is quite large considering that this is a naturalistic clinical trial, and it has been calculated from power considerations for the primary outcome (WSAS). As of 20 September 2023, inclusion of participants had reached 50%; therefore, the research team is analysing baseline data from the self-reports for first half of the participants (*n* = 294), medical record data for the participant before randomisation, and data from therapists at T1 concerning their descriptive assessment of the life areas which are seen as part of the participant’s current situation and data. The goal is to describe the features of the sample as a whole. Depending on the amount of time left before inclusion is complete, the research group may study self-reported data from participants at T1 (WAI-S and SRS) and compare these variables between the groups; if this happens, corresponding analyses will be performed on the entire dataset when available and presented in a later article. No data related to primary or secondary outcomes at T2–T6 will be analysed before inclusion is complete. Baseline characteristics of the randomised groups will also be presented for the full sample after inclusion is complete. *P*-values < 0.05 will be considered statistically significant. No formal adjustments of multiple testing will be performed, due to multiple secondary endpoints, but the issue will be kept in mind when interpreting the results.

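### The primary WSAS analysis may leave the mixed model by judgement after data inspection, for fallbacks that lose its missing-data protection and contradict the promise to use everyone's data

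*Protocol article*

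**What the plan says.** Under Primary outcome measure, the protocol article states: "The study’s primary outcome is change in perceived function from baseline to 12-month follow-up, measured by the" WSAS. Under Statistical analyses, the arms are compared by a t-test, and "this test will be conducted within the framework of linear mixed models (LMM) based on data from all time points".

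The same section then opens three exits, and the primary outcome is not exempt from any of them:

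- "If the assumptions for using LMMs are not met, the analyses can be carried out as separate comparisons at the 12-month follow-up".
- Independent-samples t-tests are offered as an option on large-sample grounds.
- For rank-based methods, the rule reads: "Non-parametric tests will be used if they are considered more appropriate after the distribution of the data is inspected".

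The only check described is that residual normality "will be assessed using visual inspection of histograms and normal QQ plots". On missing data, the section says "the LMMs allow for missing outcome data at one or more occasions as long as data are missing at random (MAR"), and concludes from this that every participant's data will enter the primary analyses. The Power and sample size calculation section adds: "If we estimate a drop-out of 40%, we thus need 294 in each group".

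**The concern.** The LMM is clearly named first, but the rule for leaving it is open. No criterion says when its assumptions have failed or when a rank test becomes more suitable, and nothing says that this judgement is made without sight of allocation. This is not a detail left to an analysis plan, because the article itself states the rule.

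The exits also lead to something weaker. The missing-data argument belongs to maximum likelihood in the LMM and does not carry over to a separate comparison at 12 months, for which no imputation or weighting is described. A rank test addresses a different quantity from the one used to size the trial. It is also unclear whether the fallback would compare 12-month scores or change from baseline. At stake are the population and the quantity behind the headline result, in a trial that plans for 40% drop-out.

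**Working it through.** **1. The plan's own figure.** Inputs from Power and sample size calculation: difference 3, SD 10, power 80%, significance level 0.05 (taken as two-sided).

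- n per arm = 2(z₀.₉₇₅ + z₀.₈₀)² SD²/Δ² = 2 × (1.960 + 0.842)² × 100/9 = 2 × 7.85 × 100/9 ≈ 174.4, so 175. Solving for the t-test gives 175.4, so 176.
- 176/0.6 = 293.3, so 294 per arm and 588 in total. The plan's figure reproduces.

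**2. Who is analysed under the fallback.** 588 × 0.6 = 352.8, about 353 participants observed at 12 months. 588 − 353 = 235 are left out. This cannot be squared with the statement that everyone's data are included.

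**3. What each option estimates.**

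| Option | Data used | Target |
|---|---|---|
| LMM contrast | All visits, all participants | Difference in mean change, valid under MAR |
| Separate t-test | Those observed at 12 months | Difference in mean score or mean change (not stated) among those observed |
| Rank test | Those observed at 12 months | Distributional shift or probability of superiority, not a mean difference |

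**4. The trigger.** The section relies on the central limit theorem to defend the t-test in a large sample. The LMM's 12-month contrast is also a large-sample estimate, so the same argument supports it equally. Non-normal residuals are therefore no reason to exchange the LMM for a t-test.

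**5. Size of the bias.** The article gives no visit correlations or dropout model, so these are assumptions. The simulation had 294 per arm, visits at baseline and 2, 4, 8 and 12 months, SD 10, correlation 0.6 between visits, and no true effect. At each visit the log-odds of dropping out were −2 + g × (previous score − 20)/10. Total loss was 40% to 44% per arm, with 1,500 trials per row. Entries are EaT minus TAU in WSAS points.

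| g in TAU, EaT | Likelihood estimate, change | Observed only, 12-month score | Observed only, change | t-test rejection, score / change |
|---|---|---|---|---|
| 0.8, 0.8 (same) | −0.02 | −0.02 | 0.00 | 5.6% / 4.6% |
| 0.8, 0 (TAU only) | 0.01 | 2.31 | −0.43 | 57.3% / 8.3% |
| 0.8, −0.8 (opposite) | −0.02 | 4.55 | −0.78 | 99.0% / 12.8% |

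Separate runs assumed a baseline-to-12-month correlation of 0.45 and opposite slopes of ±0.3 and ±0.6 per 10 points. They gave 12-month-score biases of 1.43 and 2.90 (rejection 28.0% and 77.7%) and change-score biases of 0.36 and 0.75 in size (6.5% and 9.7%). The LMM was off by −0.06 and 0.01 (5.3% and 4.4%). A further run gave about 0.9 to 3.5 for scores and 0.2 to 0.8 for change. Taken together, the range is roughly 1 to 5 points for scores and 0.2 to 0.8 for change.

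**6. Type I error from choosing a test, no effect and no selective dropout.**

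- Smallest p-value among LMM, t-test and Mann-Whitney: 8.8%.
- Smallest among 12-month t-test, Mann-Whitney and a baseline-adjusted test: 8.7%.
- Smallest among five candidate tests: 11.2%.
- Smallest of t-test and Mann-Whitney on change scores only: 5.5%.
- Switch from t-test to Mann-Whitney on distribution shape alone (Shapiro p < 0.2 on pooled residuals, an assumed trigger): 5.0%.

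**The case against.** Several stronger readings are tempting, and the article does not support them.

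- *The test is chosen on unblinded data.* The article says that the trial is non-blinded and that participants and therapists cannot be blinded. It does not say that the analyst sees allocation when inspecting distributions, and pooled residual plots show no arm difference. What stands is the silence on the point.
- *Type I error will be about 9%.* That requires picking the smallest p-value. The stated trigger is distribution shape, and a shape-based switch from t-test to rank test left the error at 5.0%. That check does not cover the step from the LMM to a t-test.
- *The fallback abandons change from baseline.* The section opens by defining the primary analysis as change, so the separate comparison may well be of change scores. With complete data from a randomised trial, both versions have the same expected group difference. The text is ambiguous on this.
- *Early discharge from EaT will cause differential dropout.* Questionnaires are sent electronically at fixed months after inclusion, with reminders, so ending clinic contact does not end follow-up. Nothing in the article points to opposite dropout patterns.

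It can also be said that the fallbacks are conditional, that outcomes at T2–T6 are not analysed until inclusion is complete, that an analysis plan not shown may fix the trigger, and that 176 per arm keeps the planned 80% power. All of this is fair, and power is not the problem. But the bar on early analysis does not stop the choice being made on the final data. Nor does any of it reconcile the fallback with the statement about everyone's data.

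**Conclusion.** The point holds as a defect in a stated rule. The primary analysis can be replaced by judgement, without a threshold, by one that covers about 353 of 588 participants at the planned drop-out, loses the MAR protection and contradicts the section's own statement on inclusion. If a rank test is used, it also no longer estimates the three-unit mean difference.

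The harm is conditional. Bias appears only if dropout depends on earlier scores differently by arm. It is then large against the three-unit target if 12-month scores are compared and modest if change is compared. These sizes rest on assumed correlations and dropout slopes. The count of 353 rests on the planning rate of 40%, and on reading a separate comparison with no stated imputation as one of observed participants only.

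**What to change.** In Statistical analyses, and in any analysis plan:

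1. Name the LMM contrast in change from baseline to 12 months as the sole primary analysis, whatever the residual plots show.
2. If residuals look non-normal, keep the same estimate and use robust (sandwich) or participant-bootstrap standard errors.
3. Relabel the separate t-tests as supportive, stating that they compare change from baseline among those observed at 12 months. Relabel the rank tests as supportive too.
4. Lock this before T2–T6 outcomes are analysed, and carry out any model checks blind to allocation.

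If an analysis plan already fixes these points, the article's fallback sentences should be brought into line with it. The cost is a few sentences and slightly more analysis work. No extra data are needed and the sample size stays at 588.
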